## Abstract

**Background:**

Current smoking cessation treatments focus on addressing the pharmacological dependence of smokers on nicotine. However, new strategies are needed that address both nicotine dependence and the psychological dependence on cigarettes as the source of nicotine. Evidence from a number of small smoking cessation studies suggests that the use of cigarettes with reduced nicotine content, in combination with nicotine replacement therapy (NRT), may help reduce withdrawal symptoms and increase quit rates. This paper describes the protocol for a large randomised-controlled trial to test the effect of using nicotine-free cigarettes together with NRT on long-term quit rates.

**Methods/design:**

This single-blind, randomised trial aims to recruit 1,410 participants through the national telephone-based Quitline service in New Zealand. Participants in the treatment arm will be asked to stop smoking nicotine-containing cigarettes on their chosen Quit day and smoke *ad libitum *nicotine-free (Quest 3) cigarettes for six weeks. At the same time people in this group will be asked to start using NRT patches, gum and/or lozenges (as recommended by Quitline) for eight weeks. Participants in the control arm will be asked to stop smoking completely on their chosen Quit day and start using NRT patches, gum and/or lozenges (as recommended by Quitline) for eight weeks. Data collection will occur at baseline, three and six weeks, and three and six months after Quit day. The primary outcome is the proportion of participants who self-report seven-day point prevalence abstinence at six months since Quit date.

**Discussion:**

Smoking prevalence in New Zealand has changed little in recent years (particularly in Māori, the indigenous people of New Zealand) and additional options for smokers who want to quit are needed. Although a variety of methods are available to help, many are expensive, have side effects, and despite their use most quit attempts still fail. This trial will test the balance of benefits and risks of a new strategy for people to overcome nicotine dependence. Since smoking is the leading cause of lost healthy life years in New Zealand, if proven effective this strategy is likely to have substantial public health benefits.

**Trial registration:**

Australia and New Zealand Clinical Trials Register (ANZCTR): ACTRN12608000410358

## Background

Smoking is the leading cause of lost healthy life years in New Zealand. In 1990, 28% of New Zealand adults smoked, with this figure dropping to 24.9% in 1996/7, 24.5% in 2002/3 [1] and 19.7% in 2006/7 [2]. In Māori (indigenous New Zealanders) there has been little downward trend in smoking prevalence since the early 1990's, with 45.5% of Māori smoking in 1996/7, and 47.2% smoking in 2002/3 [2]. However, in 2006/7 there was a sharp fall in smoking prevalence in Māori, down to 38% [2]. Despite this recent evidence of change, based on the current rate of progress it is estimated that it will take 100 years before the adult smoking rates in New Zealand reach 3.6%, the level of all New Zealand doctors now smoking [3]. New approaches to smoking cessation are urgently needed, ideally ones that give additional benefits to existing strategies. One approach that warrants further investigation is to look at ways of reducing the association between smoking and nicotine delivery.

Nicotine is the constituent of tobacco principally responsible for the addictive nature of cigarette smoking. Reward pathways in the brain are stimulated within two to three minutes of inhalation. The smoker is compelled to continue dosing throughout the day to maintain the desirable effects of nicotine and mitigate feelings of withdrawal [4]. Other factors, besides nicotine, may also play a part in the dependency-forming aspects of smoking, including the effects of other chemicals in tobacco smoke, the strong behavioural/tactile association of smoking and the social pleasure of smoking.

There is some evidence that progressive reduction in the level of nicotine in cigarette tobacco can reduce the level of nicotine dependence in smokers, with minimal compensatory smoking and without any negative health effects [5]. Reduced nicotine cigarettes have been produced in the past (as the Quest brand marketed by Vector Tobacco Inc, USA), with the tobacco altered through genetic modification. Quest 1, 2 and 3 cigarettes have a nicotine yield of 0.6 mg, 0.3 mg and ≤0.05 mg per cigarette respectively, an average nicotine content of 8.9 mg, 5.1 mg and 1.0 mg per cigarette respectively, and a tar content of 10 mg per cigarette (similar to the level in regular cigarettes). These cigarettes are no longer commercially available, but are available for research purposes. The use of Quest 3 cigarettes, so called nicotine-free cigarettes, warrant further scientific investigation, as current evidence suggests that the use of nicotine replacement therapy (NRT) in combination with such cigarettes may have a greater impact on the signs and symptoms of withdrawal and cessation rates, compared to the use of nicotine-free cigarettes alone [5]. However, there is a need to undertake adequately powered clinical trials to clarify the true strength and direction of the above association, with at least six months follow-up data collected.

## Methods/design

### Objectives

The primary objective of this trial is to determine the combined effect of nicotine-free cigarettes and NRT (used immediately after quitting), on long-term quit rates. Secondary objectives include whether such an intervention is cost effective and acceptable.

### Study design

This study is a parallel, randomised controlled clinical trial, with allocation concealed from the study researchers.

### Study population

The study population will be registered and eligible callers to the national toll-free Quitline cessation service.

### Inclusion criteria

Participants will be smokers from throughout New Zealand who want to stop smoking. Participants will be eligible provided they: are at least 18 years of age, have their first cigarette within 30 minutes of waking, are able to provide verbal consent, and have a telephone.

### Exclusion criteria

Pregnant women and women who are breastfeeding will be excluded from the trial. People will also be excluded from the trial if they meet any of the following criteria: current users of NRT products; current clients of Txt2Quit and NRT Online (current Quitline services); current users of non-nicotine based cessation therapies (e.g. buproprion, clonidine, nortriptyline or varenicline); they only use non-cigarette tobacco products (e.g. pipes, cigars); they have had a myocardial infarction within the last two weeks; and have had angina, severe cardiac arrhythmia or a stroke in acute phase within the last two weeks. The medical conditions above are listed contraindications for the use of NRT patch, gum, and lozenge. A number of disease conditions are known where precautions for the use of NRT products are indicated, such as severe cardiovascular disease (occlusive peripheral arterial disease, cerebrovascular disease, stable angina pectoris, and uncompensated heart failure) and vasospasm, uncontrolled hypertension, renal or hepatic impairment, active duodenal ulcers and gastric ulcers. Quitline staff will ask potential participants about these conditions, prior to participant randomisation.

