### Baseline assessments

Participants from throughout New Zealand will call Quitline seeking advice and wishing to enrol in the Quitline smoking cessation programme. A Quit advisor from Quitline will undertake the standard Quitline assessment. A list of those individuals who indicate that they wish to take part in research will be transferred from the Quitline database to the trial research assistants based at Quitline. The research assistants will attempt to make contact with people on the list. Those contacted will be told about the trial and asked if they would like to participate. If the potential participant indicates that they are interested, they are consented and asked for demographic data (age and sex) and checked to see if they meet the inclusion criteria for the trial. For those that do meet the inclusion criteria, further details will be collected about the participant's ethnicity and level of nicotine dependence (as determined by the FTND Questionnaire [6]) and they will be randomised Data from this initial assessment will then be electronically transferred (securely) to the Clinical Trials Research Unit's Oracle database. The research assistant will then collect the following baseline data from each participant over the telephone.

• Demographic information: Socio-economic position, based on income, education and occupation.

• Smoking history: Age when started, number of cigarettes smoked per day, number of years as regular smoker, number of previous unsuccessful attempts to give up in past 12 months and the method used, other types of smoking (pipe, cigar), usual brand/pack size (and how long pack lasts), and type of cigarettes smoked per day (e.g. roll-your-own or factory-made).

• Other smoking related information: Self-rated chances of quitting (measured on a scale of one to five, where one is very low and five is very high), household smoking, smoking in cars.

• Concomitant medication: Information about types of medication currently used will be collected.

• The physical signs and symptoms associated with withdrawal: Measured using the Mood and Physical Symptoms Scale (MPSS) [7]. Additional withdrawal questions will also be asked related to the frequency of disturbed sleep, anxiety, mouth ulcers, cough, impatience, dizziness and increased dreaming [8].

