### Outcome measures

#### Primary outcome

The proportion of participants who self-report having stopped smoking at six months after their Quit date. 'Stopped smoking' will be defined as having consumed no nicotine cigarettes (not a single puff) in the previous seven days (seven-day point prevalence).

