#### Secondary outcomes

The following secondary outcome measures will be assessed at three and six weeks after the Quit date in the treatment group only:

• Information related to the use of the nicotine-free cigarettes: Participants will be asked for their views on the use of the nicotine-free cigarettes (including concerns, whether they liked the taste of them, etc), and whether the six weeks use of the cigarettes was adequate. The number of nicotine-free cigarettes and normal cigarettes smoked each week during the intervention period will also be recorded.

• Information related to the use of the NRT: Participants will be asked about their use of NRT during the treatment period.

The following secondary outcome measures will be assessed in all participants at three weeks, six weeks, three months and/or six months after the Quit date:

• The physical signs and symptoms associated with withdrawal at three and six weeks: Measured using the Mood and Physical Symptoms Scale (MPSS) [7]. Additional withdrawal questions will also be asked related to the frequency of disturbed sleep, anxiety, mouth ulcers, cough, impatience, dizziness and increased dreaming [8].

• Self-rated chances of quitting at three and six weeks: Measured on a scale of one to five, where one is very low and five is very high.

• Proportion of participants who have stopped smoking at three weeks, six weeks and three months: Defined as no nicotine cigarettes (not even a puff) in the past seven days.

• Continuous abstinence: Defined as self-report of smoking no more than five nicotine cigarettes from the Quit date, collected at all time points.

• Proportion of participants who have significantly reduced daily smoking level at six months: Defined as reducing consumption by at least 25% (in terms of numbers of cigarettes per day or weight of loose tobacco per day).

• Number of cigarettes currently smoked per day: If the participant is still smoking (all times points). Pack size (and how long pack lasts) if smoking roll-your-owns.

• Cost information: Cost outcomes will include cost per quitter, cost per person reducing their daily cigarette consumption, and cost per Quality Adjusted Life Year of life saved among quitters. The tobacco expenditure savings to individual smokers will also be calculated using data on the daily amount smoked prior to quitting and the price of the particular products smoked.

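### The abstinence outcomes count only nicotine cigarettes, so a participant who still smokes, or switches to, pipes or cigars is scored as having stopped smoking

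*Protocol article*

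**What the plan says.** **Entry.** Under Inclusion criteria, participants must "have their first cigarette within 30 minutes of waking"; nothing is said against using other tobacco as well. Under Exclusion criteria, people are left out on tobacco type only when "they only use non-cigarette tobacco products (e.g. pipes, cigars" applies.

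**Baseline.** The smoking history in Baseline assessments includes "other types of smoking (pipe, cigar" use.

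**Outcomes.**
- Primary outcome, six months: "having consumed no nicotine cigarettes (not a single puff) in the previous seven days".
- Secondary outcome, stopped smoking at three weeks, six weeks and three months: "Defined as no nicotine cigarettes (not even a puff) in the past seven days".
- Secondary outcome, continuous abstinence: "Defined as self-report of smoking no more than five nicotine cigarettes from the Quit date".

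Quit day, in the Study intervention section, is also tied to cigarettes that contain nicotine. One secondary outcome uses a wider measure: the 25% reduction outcome is expressed "in terms of numbers of cigarettes per day or weight of loose tobacco per day". It does not decide who is scored as having stopped.

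**The concern.** The primary objective concerns long-term quit rates, and the outcome carries the label of having stopped smoking. The rule behind that label ignores two smoked tobacco products that the protocol itself names at entry and at baseline. A person smoking cigars every day at six months satisfies it.

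This affects ordinary tobacco products in both arms. It is a separate matter from how the supplied Quest 3 cigarettes should be counted.

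Three results would carry the error: the quit rate in each arm; the comparison between arms, if such users are unevenly spread; and the cost per quitter and cost per quality-adjusted life year among quitters, which credit health gains to people who may still be smoking. The cost analyses are planned only if the primary outcome differs statistically between groups, so the last consequence is conditional.

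**Working it through.** **Step 1: the entry rules against each outcome definition.**

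| Participant at six months | Eligible at entry? | Nicotine cigarettes in past seven days | Scored as stopped? |
|---|---|---|---|
| Smoked cigarettes only, now smokes nothing | Yes | None | Yes, correctly |
| Smoked cigarettes and cigars, now cigars only | Yes, since not an exclusive user | None | Yes, incorrectly |
| Smoked cigarettes only, now a pipe | Yes | None | Yes, incorrectly |

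The same holds at three weeks, six weeks and three months, and for continuous abstinence, because all use the same unit. Time to first lapse is named under Treatment effects without a definition of lapse, so the statement covers the abstinence outcomes that the article defines.

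**Step 2: the planned sample size, as a reference.** The Sample size section gives 705 per group, 20% loss, 90% power, p = 0.05 and a 7.5-point difference, but no control rate. With the pooled two-sided formula

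n = [1.96·√(2·p̄·(1−p̄)) + 1.2816·√(p1(1−p1) + p2(1−p2))]² / (p2−p1)²

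and assumed rates of 15% and 22.5% (p̄ = 18.75%):
- first term: 1.96 × √0.3047 = 1.082
- second term: 1.2816 × √0.3019 = 0.704
- n = 1.786² / 0.075² = 568 per group after rounding up
- with 20% loss: 568 / 0.8 = 710

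Control rates of about 14.2% to 15.5% come within 3% of 705. With a continuity correction the range is about 13.1% to 14.4%. The stated size is therefore attainable, and nothing here shows it to be wrong.

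**Step 3: how far the misclassification could move the result.** The article gives no prevalence of dual use, so these are illustrations.

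*(a) The same number of points, x, added to both arms.* (p2 + x) − (p1 + x) = p2 − p1. Each quit rate is too high by x; the difference is unchanged.

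*(b) The same share, f, of scored quitters in both arms still smoking pipes or cigars.* The true difference is 7.5 × (1 − f). Assumed scored control rate 14%; evaluable per group 705 × 0.8 = 564. The last column is the power for abstinence that counts pipes and cigars as smoking.

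| Share f | True difference (points) | Power |
|---|---|---|
| 0 | 7.5 | 91.0% |
| 1% | 7.5 × 0.99 = 7.4 | 90.7% |
| 5% | 7.5 × 0.95 = 7.1 | 89.3% |
| 10% | 7.5 × 0.90 = 6.75 | 87.3% |

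**The case against.** **The article is condensed, and the full protocol and case record forms are not shown.** This stands for the follow-up questions. The listed follow-up items name no pipe or cigar question, but the forms may contain one, so its absence cannot be asserted. It does not rescue the definitions. They are stated explicitly: an analysis that follows them scores these people as quitters, and one that does not would depart from them.

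**The wording serves a purpose.** Restricting the count to nicotine cigarettes matches the Quit day definition and keeps the supplied Quest 3 cigarettes apart from ordinary ones. This also stands. A blanket rule of no smoked tobacco would score use of the allocated product as failure at three and six weeks, and would override the allowance of up to five cigarettes in continuous abstinence. Any rewording must avoid both.

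**The effect is small.** Probably so. Entry requires an early-morning cigarette, and nothing suggests that pipe or cigar use is common in this population.

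**A stronger reading to avoid: bias in a known direction.** A reader might infer that controls, having no substitute to smoke, would turn to other tobacco more often, so that the trial understates the treatment effect. With assumed shares of 3% of controls and 1% of the treatment arm, a true 7.5 points would be seen as 7.5 − (3 − 1) = 5.5. The documents do not support this. Quest 3 use ends at six weeks, whereas the primary outcome covers the seven days before six months, when neither arm has a supplied substitute. Reversing the assumed shares would give 7.5 + 2 = 9.5, and the article favours neither. Three points would also be about one in five scored control quitters (3/15.5 = 19% to 3/14.2 = 21%), which is extreme.

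**Conclusion.** The definitional error stands. All the defined abstinence outcomes, the primary one included, score a current pipe or cigar smoker as having stopped, and the entry rules admit people to whom this can apply.

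The direction for each arm's quit rate, and for the count of quitters, is upward. The size is unknown and probably small. The illustrations rest on an assumed control rate and assumed shares; up to a 5% share among scored quitters in both arms, the difference changes by less than half a point. No direction of differential bias at six months is established.

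A reader might also infer that the exclusion criterion is at fault, or that dual users were admitted on purpose. The text shows only that they are admitted. Admitting them is workable; the fault lies in the outcome definitions.

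**What to change.** Under Primary outcome and Secondary outcomes, reword the point prevalence and continuous abstinence definitions so that smoking any nicotine-containing tobacco product other than the supplied trial cigarettes counts as smoking. Name factory-made cigarettes, roll-your-own cigarettes, pipes and cigars. Leave the status of the trial cigarettes and the five-cigarette allowance as the protocol sets them.

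Make sure that the baseline question on pipe and cigar smoking is repeated at every follow-up call in both arms. The outcome is self-reported by telephone, so an answer not asked for at the time cannot be reliably recovered later, even for a sensitivity analysis.

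Leave the entry criterion unchanged. The cost is a short change of wording, one brief question per call, and possibly a slightly lower quit rate in both arms.

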### Randomisation: allocation concealment and sequence generation

All potential participants will be assigned a unique registration number allocated by a central computer following details submitted on a web-based form. This number will be used to identify each randomised participant who has consented to take part. Participants will be randomised by computer, with stratified minimisation by sex, ethnicity (Māori, non-Māori), and level of nicotine dependence (> 5 points, ≤ 5 points on the Fagerström Test of Nicotine Dependence (FTND) Questionnaire [6]), to ensure a balance in these key prognostic indicators between the intervention and control group.

### Blinding

Due to the nature of the intervention only single blinding (of researchers, not of participants) is possible in this trial. Members of the trial steering committee, management committee, and other team members from the Clinical Trials Research Unit (with the exception of the project co-ordinator and the Quitline research manager) will remain blinded to treatment allocation until the code is broken (after the last follow-up call is completed and the data recorded). The project co-ordinator will not be blinded as they will be responsible for distributing the nicotine-free cigarettes to participants. The research manager and research assistants based at Quitline will not be blinded to treatment allocation, as they are required to know which group each participant has been allocated to in order to conduct the scheduled follow-up calls.

### Study intervention

Participants will be randomised to a six week intervention of nicotine-free cigarettes (Quest 3) plus eight weeks of usual care (NRT plus behavioural support) *versus *eight weeks of usual care (NRT plus behavioural support).

• Treatment group: Participants allocated to the treatment arm will be asked to stop smoking their normal cigarettes on their chosen Quit day and switch to the nicotine-free cigarettes (Quest 3) couriered to them, then at six weeks to stop smoking the nicotine-free cigarettes (Figure 1). Participants will be told that they should try all the techniques suggested by the Quitline advisors to help them get through the withdrawal period (i.e. drink water, deep breathe, do something else, delay), but if they still feel they must have a cigarette, they should only smoke the nicotine-free cigarettes provided. Participants will also be supported by Quitline in the usual way for eight weeks, with counselling/advice and NRT in the form of a patch, gum and/or lozenge (Figure 1). The Quest 3 cigarettes used in this trial have recently been reformulated by Vector Tobacco Inc and no longer contain genetically modified tobacco. The "new" cigarettes still have a similar nicotine content (1.5 mg per cigarette) and yield (≤ 0.05 mg per cigarette) as the original Quest 3 cigarettes, but the tar content has been reduced from 10mg to 4mg per cigarette. In order to verify the nicotine and tar content of the trial cigarettes, independent verification will be undertaken by Labstat Canada. Specifically, the nicotine content of the unburnt nicotine-free cigarettes will be assessed (including analysis of nicotine alkaloids by gas chromatography and tobacco moisture), as will total particulate matter, water, nicotine, particulate matter (water and nicotine free), carbon monoxide and puff number.

**Figure 1 F1:**
[figure not shown]
**Schematic of treatment allocation during intervention period**.

• Control group: Participants allocated to the control arm of the trial will be asked to stop smoking completely on their chosen Quit day and will be supported by Quitline in the usual way for eight weeks, with counselling/advice and NRT in the form of a patch, gum and/or lozenge (Figure 1).

Current standard cessation practice at the New Zealand Quitline (as at December 2010) is as follows (other cessation providers in New Zealand do not follow the process outlined here): Quitline issues by post, a Quit Card (with a 90 day expiry) for eight weeks supply of up to three NRT products (patch, gum and/or lozenge) and makes routine support calls by telephone over eight weeks. These support calls are administered by the Quitline advisors as required. Quitting support generally involves an average of three follow-up telephone calls, each lasting about 10-15 minutes. However, if people do not wish to receive support calls, they are not scheduled but callers are advised that they can phone Quitline at any time for support. Participants are advised to take the Quit Card to a pharmacist in exchange for subsidised patches, gum and/or lozenges (NZ$3 per item per four-week course of NRT). The strength of NRT patch, gum, and/or lozenges to be used by each participant is determined by the Quitline advisor (as per their dosage guidelines) as to the degree of each person's nicotine dependency. "Quit day" in this study will refer to the day each participant stops smoking cigarettes containing nicotine.

